
#### Discontinuation Criteria

Participants will be discontinued from the study if they experience clinically significant worsening depression symptoms (50% increase in HDRS-24 scores from baseline on 2 consecutive ratings); require in-patient hospitalization due to the presence of clinically significant suicidal ideation with imminent intent or attempted suicide; develop clinically significant worsening of mood, psychotic, or physical symptoms (assessed by a study physician); miss more than 2 consecutive treatments during the study; develop any medical illness that may be unstable; experience a seizure; become pregnant; or withdraw consent.

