#### Consent to Participate

Informed consent will be obtained from each individual who agrees to participate in the trial prior to and throughout participation. Patients meeting criteria will be referred to the study coordinator to discuss the study purpose, procedures, potential risks, and rights as research participants. Consent forms describing the study intervention, study procedures, and risks will be given to each participant, and written documentation of informed consent will be required prior to completing the initial screening visit and starting the study intervention. Once consent is obtained, the research personnel will confirm that inclusion and exclusion criteria are met before proceeding with baseline testing. Patients will be informed that they can withdraw from the study at any point. A copy of the information and consent documents will be given to the participants for their records. The informed consent process will be documented, and the form signed before the participant undergoes any study-specific procedures. The rights and welfare of the participants will be protected by emphasizing to them that the quality of their medical care will not be adversely affected if they decline to participate in this study.

Data confidentiality and confidentiality of the identities of the individuals participating in this study will be strictly maintained. Data forms that include identifying information will be kept in locked cabinets. Only the unique ID number assigned by the research coordinator will be used to represent participants during data entry, data transfer, data analysis, or other file management procedures. All information linking their identity will be kept separate from the research records. All information entered into a computer will be stored in a password-protected encrypted file format on a secure server. If any participant withdraws from the study, any research information recorded for or resulting from participation prior to the date that the participant formally withdrew consent will continue to be stored and used (in the manner described above) for research purposes (and will be disclosed by the investigators); however, no new data will be collected. Withdrawing from the study will not have any consequences for the participant. Participants' identities will not be revealed in the publication or presentation of any results from this study.

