### Statistical Analysis

#### Statistical and Analytical Plans

Baseline participant characteristics will be reported and described using summary statistics—mean and standard deviation for continuous data and number and proportion for categorical data. The primary analysis to determine if there is a statistically significant effect of intranasal ketamine on depressive symptoms will be the paired 1-tailed *t* test of the HDRS-24 score at baseline to week 4. We will also report the standardized mean difference as a measure of effect size (small: 0.2; medium: 0.5; large: 0.8 [40]). For tolerability and safety outcomes, we will report the number and proportion of individuals who experience a transient increase in blood pressure, agitation, and behavioral disturbance. To assess suicidality change, we will use the 1-tailed paired *t* test from baseline to week 4 of the Scale of Suicide Ideation score and calculate the standardized mean difference. For neurophysiology, we will use the 1-tailed independent *t* test to compare components of TMS-evoked responses at left dorsolateral prefrontal cortex. In addition, we will use the nonparametric cluster-based permutation test to investigate any significant changes in overall EEG channels.

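### Participants who worsen leave the study, not only treatment, so as written the baseline-to-week-4 paired tests lose them and would lean toward benefit, by an amount set by an unknown discontinuation rate

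*Protocol article*

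**What the plan says.** The Discontinuation Criteria section of the protocol article opens: "Participants will be discontinued from the study if they experience clinically significant worsening depression symptoms (50% increase in HDRS-24 scores from baseline". The rise has to be seen at two ratings in a row. The same sentence adds participants who "require in-patient hospitalization due to the presence of clinically significant suicidal ideation with imminent intent or attempted suicide", and those who "develop clinically significant worsening of mood, psychotic, or physical symptoms (assessed by a study physician"). It also lists missed treatments, unstable medical illness, seizure, pregnancy and withdrawal of consent. All of these end participation in the study; stopping treatment is not distinguished from stopping assessment.

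Under Statistical and Analytical Plans, the primary analysis of depressive symptoms "will be the paired 1-tailed *t* test of the HDRS-24 score at baseline to week 4", reported with a standardised mean difference. Suicidality is handled the same way, by a one-tailed paired "test from baseline to week 4 of the Scale of Suicide Ideation score and calculate the standardized mean difference".

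On data after exit, the article speaks only of participants who withdraw. Under Consent to Participate, the sentence about information recorded before withdrawal reads, in part, "will continue to be stored and used (in the manner described above) for research purposes (and will be disclosed by the investigators); however, no new" (it ends by ruling out any later data collection). It does not say whether a participant discontinued for worsening, who still consents, is rated at week 4.

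**The concern.** Leaving the study depends on the outcome being analysed. One trigger is a rise on HDRS-24 itself, and two others (suicidality admission, clinical worsening of mood) are close relatives of the two scales tested. A paired t test uses only people with both scores. If worsening participants leave before week 4, the people most likely to show a poor result are the ones missing, and the direction of the error is predictable.

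At stake are the mean HDRS-24 change, its standardised mean difference and the one-tailed p value. The article says the results will inform a larger, adequately powered randomised trial, so an effect size that is too favourable could lead to a trial that is too small. In the suicide-ideation test, the cases under-represented would be those severe enough to lead to admission.

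**Working it through.** **The plan's own figure.** The Sample Size section gives 25 participants from recruitment alone: 250 per year × 25% × 20% × 2 years = 25 (30 at 30%). The figure reproduces. It carries no SD, alpha, power or allowance for discontinuation, so the documents give no rate from which to compute the bias. What follows rests on stated assumptions.

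**Step 1: who can be lost.** Eligibility requires HRSD-24 above 14, so a 50% rise is at least 0.5 × 15 = 7.5 points. A participant whose second qualifying rating falls before week 4 leaves without a week-4 score. If the second rating is the week-4 rating, the score exists and nothing is lost.

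**Step 2: arithmetic.** Let k of 25 be removed with change w, and let completers have mean change m. The all-treated mean is ((25 − k)m + kw)/25, so the completer bias is k(m − w)/25.

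- Assumed baseline 25, m = −5, w = +12.5: the bias is k × (−17.5)/25 = −0.7, −1.4, −2.1 and −3.5 points for k = 1, 2, 3 and 5.
- Assumed baseline 30, m = −8, completer SD 8, w = +15 with no spread. The all-treated SD is √{[(24 − k) × 64 + (25 − k)k × 23²/25]/24}. Here the standardised change is mean change divided by SD of change.

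| k removed | All-treated mean | SD | Standardised change |
|---|---|---|---|
| 0 (completers only) | −8.0 | 8.0 | 1.00 |
| 1 | −7.08 | 9.08 | 0.78 |
| 2 | −6.16 | 9.96 | 0.62 |
| 3 | −5.24 | 10.69 | 0.49 |

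These are conditional illustrations. They place every removed participant at the 50% threshold and say nothing about how often that happens.

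**Step 3: simulation of the rules.** 25 participants per trial, 10,000 trials per scenario. Assumptions not in the documents: weekly ratings; baseline mean 27, SD 6, floor 15; SD of week-4 change 7 or 10, with 70% of that variance a personal trend and 30% rating noise; one-tailed alpha 0.05. The 50% rule is applied to consecutive ratings in weeks 1 to 3. The broader triggers are represented by discontinuing none, half or all of those with a week-3 rise above 5 points. With a true change of 0:

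| SD | Broader triggers applied to | Discontinued | Completer mean change | One-tailed error |
|---|---|---|---|---|
| 7 | none | 0.2% | −0.03 | 5.2% |
| 7 | half | 9.9% | −0.7 | 11.7% |
| 7 | all | 19.7% | −1.5 | 26.8% |
| 10 | none | 1.3% | −0.2 | 5.7% |
| 10 | half | 14.4% | −1.3 | 15.0% |
| 10 | all | 27.5% | −2.9 | 37.4% |

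With week-4 scores kept for all 25, the mean was close to 0 and the error about 5% throughout. With a true change of −5, completers averaged −5.04 to −5.06 under the 50% rule alone, and −5.3 to −6.7 with the broader triggers, which then removed 3.4% to 14.7%. The bias was toward benefit in every scenario.

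**The case against.** The strongest reply is that a completers-only analysis is nowhere stated. A reader might infer that the paired test definitely uses only those who remain and that the recorded worsening can never enter it. The article does not say so. It names no completer set, rules out no imputation or carry-forward, and keeps earlier data of those who withdraw for use. The analysis plan and the visit schedule (Multimedia Appendix 2) are not shown, and either may contain a missing-data rule or an early-termination rating. This stands, and it makes the point conditional. It does not remove it: an analysis plan can say how to treat a missing week-4 rating but cannot recover one that was never taken, and exit from the study is what the article does state.

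A second reply is that the 50% rule is strict and on its own barely matters. That also stands. Material bias needs the broader triggers, at rates the documents do not give. Several listed reasons, such as pregnancy or missed treatments, need not be related to mood.

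A reader might also infer that worsening suicidality cannot show in the suicidality analysis. That goes too far. Worsening that meets no discontinuation trigger stays in the paired test, the Scale of Suicide Ideation is given weekly, and serious adverse events are reported separately where reporting requirements are met.

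Finally, this is an uncontrolled pilot whose primary outcome is feasibility, and the Discussion says statistical significance is not the goal. That limits the consequence. Yet the statistical section calls this test the primary analysis and promises an effect size.

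**Conclusion.** The point holds in conditional form. Followed as written, the plan makes week-4 scores missing because of the outcome, and the paired estimates would lean toward benefit unless a rule not shown here brings the discontinued participants in. The direction is clear; the size is not. It is negligible if only the 50% rule operates. It is about 0.7 to 2.9 HDRS-24 points, with one-tailed error of 12% to 37% instead of 5%, if the broader triggers remove 10% to 28% and there is no true change. With a true change of −5, the corresponding overstatement is about 0.3 to 1.7 points. All of these rest on the assumed rates, SDs and weekly ratings above. No figure was derived for the suicide-ideation test, where the conclusion is only that suicidality leading to hospitalisation is under-represented. The change is worth making because it is cheap and must be in place before participants reach week 4.

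**What to change.** Leave the clinical stopping criteria exactly as they are, but state that they end study treatment and not outcome assessment. Keep the week-4 HRSD-24 and Scale of Suicide Ideation ratings for every dosed participant who has not withdrawn consent.

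Base the main estimate on all dosed participants and all recorded ratings, including those that triggered discontinuation. A repeated-measures model is one reasonable choice among several. It suits the HDRS-24 trigger because the scores that cause exit are observed. It is less secure for admission or physician-judged worsening between ratings, which is why the retained week-4 rating matters. Add a sensitivity analysis using the last score before discontinuation, and report the completer paired t test as supportive, with the number discontinued and the reasons.

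The cost is a wording change, one retained assessment for a few participants and slightly more analysis. The estimate may become less favourable.

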Ketamine, a noncompetitive high-affinity *N*-methyl-D-aspartate (NMDA) receptor antagonist, has been shown to exert rapid and robust antidepressant effects in patients with treatment-resistant depression [8]. Studies have demonstrated that a single intravenous infusion of an NMDA antagonist resulted in significant decreases in depressive symptoms [9], making ketamine an attractive treatment option with the ability to simultaneously reduce neuronal activity in the limbic and subcortical regions while increasing activity in the prefrontal cortex [10], an area of core dysfunction reported in those with depression [10]. Numerous studies [11,12] have demonstrated that a subanesthetic dose of ketamine (0.5-0.8 mg/kg) over 40-minute intravenous infusion produces rapid antidepressant effects in patients with treatment-resistant depression. It has also been reported that the route of administration of ketamine can influence the clinical antidepressant effects of treatment owing to its extensive first-pass metabolism; specifically, the highest bioavailability of ketamine is achieved via intravenous infusion, while oral administration yields the lowest bioavailability [13]. Findings suggest that 70% of patients with treatment-resistant depression respond to 1 to 3 administrations of ketamine, and 30% to 60% of patients with treatment-resistant depression experience remission of their depressive symptoms. Research suggests that most responses occur if ketamine is administered in 6 or more sessions over a >2-week period [8,12].

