#### Drug Administration and Scheduling

Intranasal rketamine will be administered twice per week for 4 weeks (8 treatment sessions in total). The dosage schedule will be determined based on participants’ weight, clinical response, and tolerability (Multimedia Appendix 1). Given that the absolute bioavailability of intranasal ketamine is 45% to 50 % compared with that of intravenous administration [13,14], intranasal doses will range from 1 mg/kg to 1.6 mg/kg to represent usual intravenous doses of 0.5-0.8 mg/kg and to account for reduced bioavailability of the intranasal form. Participants will be started at the lowest dose during the first treatment session (average 50 mg of intranasal ketamine administered in 2 syringes with 25 mg per syringe).

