#### Dose Adjustment

If the first session is tolerated well, and the patient has no side effects, the session 2 dose will be increased to 1 mg/kg (to represent an intravenous dose of 0.75 mg/kg adjusted to 50% bioavailability). If both sessions are tolerated well, session 3 will start on a full therapeutic dose (1.5-1.6 mg/kg to represent intravenous doses of 0.75-1 mg/kg). Participants will have a weekly visit with the study’s medical doctor, and doses will be monitored and adjusted based on tolerability and clinical response; however, they will not exceed 1.6 mg/kg.

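### The missed-session rule ends study participation, so the week-4 paired tests rest on patients who kept attending; staying in does not show that 8 sessions were delivered

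*Protocol article*

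**What the plan says.** The course, under Drug Administration and Scheduling: "Intranasal rketamine will be administered twice per week for 4 weeks (8 treatment sessions in total").

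The Discontinuation Criteria are a single list that opens "Participants will be discontinued from the study if they experience clinically significant worsening depression symptoms" and includes patients who "miss more than 2 consecutive treatments during the study". Every item in the list has the same consequence, which is removal from the study. The article has no separate category for stopping treatment while staying under assessment, and no rule on the total number of sessions missed or attended.

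Under Statistical and Analytical Plans, the main analysis of depressive symptoms "will be the paired 1-tailed *t* test of the HDRS-24 score at baseline to week 4". Change on the Scale of Suicide Ideation is tested in the same way over the same interval. The consent section stops collection of new data when a participant formally withdraws consent. It does not mention patients removed for missed sessions.

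**The concern.** A paired test uses only patients who have both scores. If the rule ends a patient's participation before week 4, that patient has a baseline score but no partner for it. Whether a patient attends can depend on benefit, side effects or mood, so those removed are unlikely to be a random subset. If they tend to be the patients doing poorly, the week-4 change looks better than it was among everyone treated. In a single-arm trial of 25 there is no control group in which a similar loss might offset this.

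The second issue is what staying in the study shows. The rule caps the length of a run of misses and not their number, so a patient can remain in after receiving a minority of the sessions. This matters because the stated primary outcome is the feasibility of a larger trial.

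**Working it through.** **Inputs from the article.** Two sessions per week for 4 weeks; removal when more than 2 consecutive sessions are missed, that is, at a run of 3; 25 participants. The article's own figures reproduce: 2 × 4 = 8 sessions, and 250 × 0.25 × 0.20 × 2 years = 25 participants.

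**Input not in the article.** The chance q of missing a session. It is assumed to be independent between sessions and set at 10%, 20% and 30%.

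**Step 1: who can stay in.** There are 2^8 = 256 patterns of attending (A) or missing (M) 8 sessions. A pattern is kept if it has no run of 3 or more M.

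| Sessions attended | Patterns kept | Patterns removed |
|---|---|---|
| 0 | 0 of 1 | 1 |
| 1 | 0 of 8 | 8 |
| 2 | 1 of 28 | 27 |
| 3 | 16 of 56 | 40 |
| 4 | 45 of 70 | 25 |
| 5 | 50 of 56 | 6 |
| 6 | 28 of 28 | 0 |
| 7 | 8 of 8 | 0 |
| 8 | 1 of 1 | 0 |

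The lowest attendance compatible with staying in is 2 of 8 (M M A M M A M M). If session 1 is always given, it is 3 of 8, for example A M M A M M A M.

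**Step 2: how many would be removed.** Let S(n) be the chance of no run of 3 misses in n sessions. Then S(0) = S(1) = S(2) = 1 and S(n) = (1−q)·S(n−1) + q(1−q)·S(n−2) + q²(1−q)·S(n−3). The chance of removal is 1 − S(8).

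| q | 1 − S(8) | Expected removed of 25 |
|---|---|---|
| 10% | 0.0055 | 0.14 |
| 20% | 0.0399 | 1.0 |
| 30% | 0.1201 | 3.0 |

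If session 1 is always given, the chance of removal is 1 − S(7), which gives 0.11, 0.84 and 2.55 of 25. Real misses tend to cluster once a patient disengages. At the same overall miss rate, clustering would make runs of 3 more common than shown.

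**Step 3: how many would stay in with 5 or fewer sessions.** Summing the kept patterns gives 0.8, 4.1 and 8.2 of 25 at 10%, 20% and 30%, or 0.5, 2.9 and 6.3 if session 1 is always given.

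**Step 4: what removal could do to the estimate.** Suppose r of 25 are removed and their true mean change is zero; this is an assumption for illustration. The mean among the remaining 25 − r then exceeds the all-treated mean by the factor 25/(25 − r). For r = 1 this is 25/24 = 1.04, and for r = 3 it is 25/22 = 1.14. If those removed had improved as much as the rest, the factor would be 1.

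**The case against.** The strongest reply is that the article does not expressly say that a patient removed for missed sessions goes unrated at week 4 or is left out of the test. Analysis sets are commonly left to an analysis plan, and the visit schedule is in an appendix that is not shown. This stands in part, because the loss of the week-4 score is a reading and not a stated rule. But it is the ordinary meaning of being discontinued from the study, and no later analysis plan can recover a rating that was never taken.

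A reader might also infer four stronger points, which the article does not support:

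- **That the rule contradicts the article's evidence on exposure.** The Introduction says that "most responses occur if ketamine is administered in 6 or more sessions over a >2-week period". The sentence before it says that 70% of patients with treatment-resistant depression respond to 1 to 3 administrations. Both are literature summary, and neither sets a minimum for this trial.
- **That the rule systematically keeps less treated patients and drops more treated ones.** A 3-of-8 pattern can stay while attending sessions 1 to 5 and missing 6 to 8 leads to removal. This is an edge case: 50 of 56 five-session patterns are kept, and nobody attending 6 or more is removed.
- **That retained patients are analysed as fully treated, or that feasibility is measured by not being discontinued.** The text says neither, and nothing prevents sessions delivered from being reported.
- **That the week-4 result no longer reflects the 8-session course.** This depends on an unknown miss rate. The only adherence information is that 3 pilot patients managed the schedule, which is weak but does not point to frequent misses.

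**Conclusion.** The concern holds in a limited form. As written, missing 3 sessions in a row ends study participation, and the paired tests to week 4 then rest on those who kept attending. The likely direction is a more favourable result, on the assumption that patients who stop attending do worse on average. The size is uncertain: about 0.1 to 3 of 25 removed at assumed independent miss rates of 10% to 30%, which is negligible at the low end and enough at the high end to matter in a sample this small.

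The enumeration rests on no assumed rate. Staying in is compatible with 3 of 8 sessions, or 2 of 8 if session 1 may be missed, so retention alone does not show that the course was delivered. The case for change rests mainly on the lost week-4 scores; the low-attendance patterns support reporting sessions delivered.

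**What to change.** State in the protocol that missing sessions does not end study participation. Unless they withdraw consent, these patients still have the week-4 HDRS-24, the Scale of Suicide Ideation and the safety assessments, and they are included in the week-4 analysis of all treated patients. Report the number of sessions delivered next to the week-4 result, so that a reader can see how much of the course the estimate reflects.

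The sponsor should reconcile the missed-session rule under Discontinuation Criteria with the 8-session course under Drug Administration and Scheduling. No stopping rule and no minimum number of sessions is proposed here.

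The cost is a change of wording, a week-4 visit for the few patients concerned, and a short table of sessions delivered. The downside is that the week-4 estimate may look slightly less favourable, because partly treated patients stay in it.
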